#### Handling of missing data.

If the missing primary endpoint data are less than 5%, all missing values will be clearly reported, with no imputation performed (given the low anticipated rate). In case the missing primary endpoint data are 5–15%, a worst-case scenario sensitivity analysis will be conducted, imputing missing data as events in the intervention group and non-events in the control group, to assess the robustness of the primary conclusion. For over 15% missing data, we will perform multiple imputation using chained equations (MICE) with predictive mean matching (PMM) based on 20 imputed datasets. The imputation model will include baseline covariates (age, sex, diabetes, sheath size, anticoagulation dose) and auxiliary variables associated with missingness. Additionally, the worst-case imputation will also be applied as a sensitivity analysis to assess robustness.

#### Descriptive statistics and baseline comparisons.

Continuous variables will be tested for normality using the Shapiro–Wilk test. Normally distributed data will be presented as the mean ± standard deviation and compared via independent samples *t*-test, whereas non-normally distributed data will be presented as the median (interquartile range, IQR) and compared via Mann–Whitney U test. Categorical variables will be presented as frequencies and percentages, with comparisons via the Chi-square test or Fisher’s exact test (as appropriate). All tests will be two-sided, with *p* < 0.05 considered statistically significant for baseline comparisons.

#### Analysis of the primary and secondary endpoints.

Statistical inference for hypothesis testing will be reserved for the primary endpoint alone, with a two-sided α level of 0.05. All comparisons of the secondary endpoints will be exploratory analyzes; their p-values and effect sizes will be for descriptive purposes and hypothesis generation only, with no formal multiplicity adjustment (e.g., Bonferroni) applied. Exploratory analyzes will also be purely descriptive in nature. Consequently, p-values and effect estimates for both the secondary and exploratory endpoints should be interpreted with extreme caution, and should not be construed as confirmatory evidence of efficacy or safety.

The primary endpoint (24-h forearm RAO incidence) will be compared between groups via Chi-square test (or Fisher’s exact test for cell counts < 5). Absolute risk difference, relative risk, and odds ratios (ORs) with 95% confidence intervals (CIs) will be calculated. Comparisons of binary secondary endpoints (e.g., vascular complications, bleeding events) will also follow the same methods. Continuous secondary endpoints (e.g., hemostasis time, active operator time) will be compared using independent samples t-test or Mann–Whitney U test, based on data distribution assessed by the Shapiro–Wilk test.

These intergroup comparisons will constitute the univariate analysis. Variables with *p* < 0.10 in these univariate analyzes, along with clinically relevant baseline characteristics (e.g., age, sex, sheath size, anticoagulation dose), will be considered for inclusion in subsequent multivariate logistic regression models to identify independent factors associated with the outcomes.

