**Fig 5 pone.0350563.g005:**
[figure not shown]
Mechanism of synchronisation with vascular repair phases. The diagram illustrates how the system’s staged decompression aligns with the three phases of vascular repair: hemostasis/thrombus stabilization (Phase A), endothelial activation/shear-stress-mediated repair (Phase B), and inflammatory clearance/remodeling (Phase C).

By integrating these innovations, the balloon pressure monitoring system aims to transform patent hemostasis from an operator-dependent art into a standardized, physiology-guided engineering process, thereby bridging the efficacy-effectiveness gap for RAO prevention.

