### Randomization, blinding implementation, and bias control

#### Randomization and allocation concealment.

The randomization sequence was generated by an independent statistician using dedicated statistical software. A blocked randomization method was adopted with randomly varying block sizes of 4 and 6, and the block size allocation was concealed from all investigators throughout the trial. Allocation concealment will be maintained via sequentially numbered, opaque sealed envelopes, which will only be opened after patient enrollment and prior to intervention assignment, thus preventing selection bias. The allocation sequence is concealed from investigators involved in enrollment and intervention assignment.

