#### Secondary endpoints.

The secondary endpoints were defined as follows:

Incidence of access-site related vascular complications, such as radial artery perforation, arteriovenous fistula, pseudoaneurysm;Incidence of bleeding events, classified per standardized bleeding scales for cardiovascular trials;Objective measures of hemostasis convenience, operationally defined to reduce measurement variability, include: i) total hemostasis time, which is the cumulative duration from arterial sheath removal to complete hemostasis device removal and puncture site hemostasis confirmation, with only active operation and assessment time counted (fixed 30/60/90-min observation periods are excluded to minimize variability); and ii) operator workforce input, which is measured via two metrics (with CRF-designed recording templates for feasibility): peak and active operator number. The peak operator number is the maximum number of healthcare personnel simultaneously performing hands-on tasks (pressure adjustment, bleeding assessment, data recording) at any stage. The active operator time is the sum of durations each operator spends on direct hands-on tasks, recorded via start/stop timestamps for each personnel.

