## Discussion

### Positioning and innovation of this study in the evidence chain

TRA is the established default strategy for coronary procedures, given its demonstrated advantages in safety and patient outcomes over transfemoral access [1,2]. Despite this, forearm RAO remains the most common procedural complication [1,2], and a significant “efficacy-effectiveness gap” persists: while optimized research protocols [1] can achieve RAO rates below 5% under controlled conditions, the real-world incidence remains as high as 33% [3]. This gap compromises the utility of the radial artery for future interventions, and originates primarily from the limitations inherent in patent hemostasis—the cornerstone of RAO prevention [2,3].

Clinically, patent hemostasis relies on operator-dependent, intermittent assessments and empirical pressure titration, leading to poor standardization, high inter-operator variability, and failure to achieve any true patency in a substantial proportion of real-world patients [2,3]. Methodologically, the existing evidence base is fragmented, characterized by a predominance of single-center or non-randomized designs, significant heterogeneity in devices and protocols, and inconsistent definitions and assessments of RAO [2,6,7]. These limitations obscure the true treatment effects and hinder the translation of research findings into practice [8,9]. Although intensive, multi-component “best-practice bundles” have achieved remarkably low RAO rates in trials, their complexity and resource demands limit their broad implementation, thus underscoring the need for a simplified, objective, and scalable approach to patent hemostasis [2,4].

The innovation of this study lies in addressing the external validity challenge [11]: traditional hemostasis’ lack of standardization decouples trial results from clinical practice. Our system bridges this gap via two core innovations to standardize hemostasis: 1) Quantitative pressure control: Replacing empirical volume-based compression with high-precision (± 3.75 mmHg) digital manometry to directly measure vascular wall pressure in real time; 2) Physiologically phased decompression: Synchronizing compression release with vascular repair stages (thrombus stabilization, endothelial activation, inflammatory clearance) via real-time bleeding status (not rigid time intervals).

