## Conclusion

This trial addresses a central paradox in interventional cardiology: specifically, the reliance on a subjective, operator-dependent technique (patent hemostasis) to protect a vessel critical for future access. By evaluating a digitally-monitored, physiology-guided compression system, we aim to demonstrate that objective standardization alone could reliably replicate the low forearm RAO rates of optimized research within real-world practice. Positive results from this trial would redefine the standard of care for radial hemostasis, shifting it from an empirical art toward a controlled engineering process, and provide a foundational evidence base for the next generation of intelligent hemostasis devices.

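### Operator dependence is the trial's stated problem and personnel are recorded, yet the exploratory time endpoints are compared without operator, and the article does not say that the hemostasis operator is named before allocation is revealed

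*Protocol article*

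**What the plan says.** **Rationale.** The Discussion (Positioning and innovation) blames reliance on intermittent operator judgement for "leading to poor standardization, high inter-operator variability". The paragraph below Fig 5 says the system is meant to "transform patent hemostasis from an operator-dependent art into a standardized, physiology-guided engineering process". The Conclusion adds "we aim to demonstrate that objective standardization alone could reliably replicate the low forearm RAO rates" as an aim.

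**Data on operators.** Under Secondary endpoints, active operator time is summed over staff and is "recorded via start/stop timestamps for each personnel". The intervention procedure records the personnel involved throughout. The control procedure mentions personnel only in connection with bleeding.

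**Allocation.** Under Randomization and allocation concealment: "A blocked randomization method was adopted with randomly varying block sizes of 4 and 6". No stratification by operator is mentioned. The envelopes are ones "which will only be opened after patient enrollment and prior to intervention assignment". The Common procedural protocol places group assignment after the coronary procedure and before any hemostatic device. Blinding implementation states that the staff performing hemostasis cannot be blinded.

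**Analysis.** Under Analysis of the primary and secondary endpoints: "Continuous secondary endpoints (e.g., hemostasis time, active operator time) will be compared using independent samples t-test", with Mann–Whitney as the alternative. 24-hour radial artery occlusion (RAO) gets a chi-square or Fisher test. The same section reserves inference for the primary endpoint and calls all secondary comparisons exploratory. The adjusted logistic models cover RAO and bleeding, and their example covariates do not include operator. Operator appears in one analysis, the learning-curve sensitivity analysis restricted to the two highest-enrolling operators, which compares early with later patients inside the intervention arm.

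**The concern.** Hemostasis time and active operator time largely measure what particular staff do. If staff differ as much as the article says, operator is a known and recorded source of variance in exactly these endpoints, and the named tests do not use it. Two things follow.

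First, precision is given away even when allocation works perfectly. Second, a selection route is not visibly closed. Once the envelope is open, unblinded staff know the arm, and the article does not say that the person who will perform hemostasis has already been named. If the choice of operator depended on arm, a difference between people would be read as a difference between devices.

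Separately, no stated analysis describes whether operators vary less under the new system, although that is the mechanism the trial proposes.

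**Working it through.** **1. The plan's own figure.** Unpooled two-proportion formula, 4.3% against 1.0%, two-sided 0.05, 80% power:

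n per arm = (0.043×0.957 + 0.010×0.990) × (1.960 + 0.842)² / 0.033² = 0.05105 × 7.849 / 0.001089, rounded up to 368, so 736 in total; 736 / 0.9 gives 818.

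Both stated figures reproduce, and this point does not touch them.

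**2. Inputs for the time endpoints.** From the article: 409 per arm. Not in the article: the number of operators, the share of variance due to operator (intraclass correlation r) and the SD. Assumed: four operators, r = 0.1 to 0.3, total variance 1.

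**3. Operator unrelated to arm.** Under individual randomization the t-test keeps its error rate. Simulation with no treatment effect gave 0.040 to 0.061 against a nominal 0.05 (6, 10 or 20 operators, r = 0.02 to 0.20, 368 per arm). With four operators and 409 per arm it gave 0.050 to 0.051. The loss is precision only. The shortening of the confidence interval from adjustment is at most 1 − √(1 − r):

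| r | Upper limit | Simulated, four operators |
|---|---|---|
| 0.1 | 5% | 4% |
| 0.2 | 11% | 8% |
| 0.3 | 16% | 12% |

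The simulated gain is smaller because four sampled operators show, on average, less spread than the population they are drawn from.

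**4. Operator mix differing by arm (hypothetical).** Let each operator's share differ between arms by d (+d, +d, −d, −d). Then

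true variance / variance used by the test = (1 − r) + r × 4d² × 409/2

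false-positive rate = 2 × [1 − Φ(1.96 / √ratio)]

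Example, r = 0.2 and d = 0.10: 0.8 + 0.2 × 0.04 × 204.5 = 2.436; √2.436 = 1.561; rate 20.9%.

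| d | r = 0.1 | r = 0.2 | r = 0.3 |
|---|---|---|---|
| 3 points | 4.7% | 4.4% | 4.1% |
| 5 points | 6.2% | 7.5% | 8.7% |
| 10 points | 13% | 21% | 27% |
| 20 points | 34% | 47% | 55% |

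The formula is approximate. Simulation with operators drawn patient by patient gave 23.9% and 51.3% at r = 0.2 for 10 and 20 points. The spread of the table is the main message: the result depends almost wholly on d, and the article gives no information on d.

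**5. RAO under the same device.** At a pooled rate of 2.65%, the SE is √(2 × 0.0265 × 0.9735 / 409) = 1.12 points. With an assumed between-operator SD of 2 points, which is large against a mean of 2.65%, the mix adds 2d × 2 points. That is 0.4 points at d = 0.10 (rate 6.5%) and 0.8 points at d = 0.20 (rate 11%).

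**The case against.** The strongest reply is that nothing here is shown to be wrong. Patients are randomized individually, so ignoring operator does not invalidate the t-test. A reader might infer from the article's silence that operators are chosen after allocation and that the error bars are therefore wrong. The documents do not support that: no section says staff are sorted by arm, and staffing at envelope opening is the kind of detail a condensed article leaves to the full protocol. This stands, and it removes any claim of actual inflation.

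It is also fair that the affected comparisons are declared exploratory and not confirmatory. There are safeguards too: supervised qualification of operators, one research nurse responsible for timestamps, and quarterly audits that include intervention assignment. The covariate and subgroup lists are given as examples, so operator could still enter the RAO and bleeding models.

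A reader might further infer that the standardization aim goes untested altogether. That is too strong. The Conclusion frames the aim as reaching low RAO rates, which the RAO comparison addresses, and between-operator variation is not a stated endpoint.

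What remains is narrower. A named test for the time endpoints leaves out a recorded source of variance, no model is stated for those endpoints, the audits and qualification do not fix who performs hemostasis before allocation is known, and the one operator analysis never compares the arms.

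**Conclusion.** The point holds in limited form and is minor. With operator unrelated to arm, the planned comparison of the time endpoints is valid and gives up some precision: at most 5–16% of interval length at r = 0.1 to 0.3, and about 4–12% with four operators, all on assumed inputs. With operator mix differing by arm, the arm difference would be confounded by operator and its standard error too small. Whether this happens, and how large it would be, cannot be read from the documents, so the false-positive rates above illustrate a range and are not findings about this trial. The primary analysis and the sample size are not called into question. The change is still worth making because active operator time is presented as a distinctive strength of the trial, and cautious reading of p-values would not remove a bias from operator mix.

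**What to change.** 1. For patients still to be enrolled, define the lead operator as the person designated to start hemostasis, and write that person's code on the CRF before the envelope is opened. A definition is needed because several staff may contribute to one patient's time.
2. Tabulate lead operator by arm.
3. Report the arm difference in hemostasis time and in active operator time, in minutes with a 95% CI, from a linear model with arm and lead operator (fixed or random effect), pooling low-volume operators. For patients whose operator may have been chosen after allocation, treat the adjusted result as a sensitivity analysis.
4. Report the between-operator SD of the time endpoints in each arm, descriptively.
5. Optional: a Mantel–Haenszel risk difference for 24-hour RAO stratified by operator, as a sensitivity analysis.

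Cost: one CRF field and a few lines of code, with no extra patients or staff. Limits: with few operators the between-operator SD will be imprecise, and because recruitment has run since September 2024, step 1 cannot help patients already enrolled.

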#### Modeling and adjusted analyzes.

Univariate logistic regression will first identify factors associated with forearm RAO and bleeding complications. The variables set for inclusion in the multivariate logistic regression model are as follows: (1) Variables with *p* < 0.10 in univariate analysis; (2) Clinically relevant baseline characteristics (e.g., age, sex, sheath size, anticoagulation dose) pre-specified based on prior literature and clinical expertise, regardless of their statistical significance in univariate analysis. A stepwise selection method (entry *p* < 0.05, exit *p* > 0.10) will be applied to establish a parsimonious model, with results reported as adjusted ORs (aORs) and 95% CIs. Multicollinearity will be assessed using the variance inflation factor (VIF), with a VIF > 5 indicating significant collinearity and necessitating model refinement.

### Prespecified subgroup and exploratory analyzes

#### 1. Subgroup analyzes.

For the primary endpoint, subgroup analyzes will be conducted for patient characteristics (e.g., age < 65 vs. ≥ 65 years, sex, diabetes status), procedural factors (e.g., sheath size 5F vs. 6F, diagnostic angiography only vs. percutaneous coronary intervention), and operational factors (e.g., compression time quartiles, minimum hemostatic pressure quartiles).

To assess for any differential treatment effect across subgroups, the interaction between the treatment assignment and each subgroup variable will be tested within a logistic regression model including terms for treatment assignment, the subgroup variable, and their interaction. Continuous variables used to define subgroups (e.g., compression time) will be categorized (e.g., into quartiles) for these analyzes. All subgroup analyzes will be exploratory, and their results should be regarded as only hypothesis-generating. Due to the risk of multiple comparisons and the absence of any formal multiplicity adjustment for interaction tests, definitive interpretations of the findings are not warranted. Continuous variables used to define subgroups (e.g., compression time) will be categorized (e.g., into quartiles) for these analyzes.

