
### Common procedural protocol

All patients underwent coronary angiography and/or percutaneous coronary intervention via a transradial approach. A uniform set of pre-procedural and intra-procedural measures, designed to minimize vascular injury and the risk of radial artery occlusion, was applied to all participants before randomization and hemostasis. This standardized protocol was implemented in accordance with contemporary best practices as established in large randomized trials [1].

Arterial Access and Procedure: Vascular access was obtained using a 6-French Glidesheath Slender introducer (Terumo, Tokyo, Japan). The choice of access side (left or right wrist) was at the operator’s discretion based on anatomical and clinical considerations. Following sheath insertion, all patients received an intravenous bolus of unfractionated heparin (5,000 IU), with additional boluses administered if needed to maintain an activated clotting time (ACT) between 250 and 300 seconds. To mitigate radial artery spasm, an intra-arterial vasodilator cocktail containing verapamil (5 mg) and/or nitroglycerin (100–200 μg) was administered through the sheath.

Pre-Hemostasis Assessment: Immediately following the coronary procedure and prior to the application of any hemostatic device (and thus prior to group assignment), patency of the access artery was confirmed using the reverse Barbeau test [17]. This step ensured a documented baseline of radial artery flow for all enrolled subjects.

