### Intervention: Operating procedure of the system

The standardized operational procedure for the balloon pressure monitoring system is summarized in Fig 4 (left panel) and detailed as follows:

Initial compression: Immediately following sheath removal, the balloon is inflated to a target pressure of 260 mmHg. (This pressure, derived from a pre-trial pilot study (n = 32), ensures reliable immediate hemostasis with no associated neurovascular or skin injuries.)Individualized minimum effective hemostatic pressure titration: The balloon pressure is gradually decreased until slight oozing is observed at the puncture site. Then, the pressure is incrementally increased in steps of 20 mmHg until bleeding ceases. This value is recorded as the patient’s initial hemostatic threshold.Phased decompression and monitoring: At 30 minutes post-procedure, the pressure is adjusted to 60 mmHg (an intermediate value based on the hemostatic threshold, with fine-tuning for bleeding status). At 60, 90, and 120 minutes post-procedure, pressure is reduced by 30 mmHg at each interval until it reaches zero.Bleeding management: If bleeding occurs at any stage, pressure is increased in 20 mmHg steps until hemostasis is reestablished.Documentation: All pressure values, operation times, and involved personnel are recorded throughout the procedure to ensure traceability.

(The parameters for this procedure—including the initial pressure, titration step, and decompression schedule—were derived from a preceding pilot study.)

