#### Operational protocol for traditional patent hemostasis.

Initial hemostasis: after sheath removal, inflate the balloon compressor with an initial 18 mL of air for primary hemostasis [2,18].Patency Confirmation (Reverse Barbeau Test): Gradually decompress the balloon until slight oozing is observed at the puncture site, then inject 1–2 mL of air to re-establish the hemostasis. Subsequently, manually compress the ulnar artery for 2 minutes while continuously monitoring the pulse oximetry waveform of the ipsilateral thumb. If the waveform remains present with a stable amplitude throughout the entire compression period (corresponding to Barbeau classification Type A or B), the radial artery patency under compression is confirmed; if the waveform disappears (corresponding to Type D or partial Type C, indicating occlusive compression), immediate further decompression must be conducted until the waveform is restored [2,18].Phased decompression: at 30 minutes post-procedure, release 1 mL of air. At 60- and 90-min post-procedure, release 3 mL of air at each interval. At 120 min post-procedure, remove the compression device [2,18].Bleeding management and documentation: if bleeding occurs, reinflate with an appropriate volume of air to achieve hemostasis, and record the time of intervention and personnel involved [2,18].

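### Two operational subgroup variables, compression time and minimum hemostatic pressure, cannot support a treatment interaction test, and the sheath-size subgroup conflicts with the common procedure

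*Protocol article*

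**What the plan says.** Under Prespecified subgroup and exploratory analyzes (1. Subgroup analyzes), the protocol article names three kinds of subgroup variable for the primary endpoint: patient characteristics (age, sex, diabetes), a procedural group, and a set of "operational factors (e.g., compression time quartiles, minimum hemostatic pressure quartiles"). The procedural group covers "sheath size 5F vs. 6F, diagnostic angiography only vs. percutaneous coronary intervention". The interaction of treatment with each variable is to be "tested within a logistic regression model including terms for treatment assignment, the subgroup variable, and their interaction". The same section calls all subgroup analyses exploratory and hypothesis-generating, and notes that interaction tests are not adjusted for multiplicity.

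Four other parts of the article bear on these variables:

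- **Common procedural protocol.** "Vascular access was obtained using a 6-French Glidesheath Slender introducer". This is part of a uniform set of measures for all participants before randomisation. Group assignment comes after the coronary procedure and before any hemostatic device is applied.
- **Intervention: Operating procedure of the system.** After oozing is seen, "the pressure is incrementally increased in steps of 20 mmHg until bleeding ceases", and the value reached is recorded as the patient's threshold.
- **Operational protocol for traditional patent hemostasis.** Control staff "inflate the balloon compressor with an initial 18 mL of air for primary hemostasis", then adjust by air volume and the oximetry waveform.
- **Handling of missing data; Analysis of the primary and secondary endpoints; Modeling and adjusted analyzes.** Sheath size is listed as a covariate in all three.

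**The concern.** A treatment-by-subgroup interaction needs a variable that is fixed before assignment, is known in both arms and takes more than one value. Two of the named variables fail one of the first two conditions, and for the third variable the article contradicts itself on the last.

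Compression time is partly a consequence of the allocated method. Patients who land in the same quartile in the two arms need not be alike, so a difference in odds ratio between quartiles may reflect who ended up there rather than effect modification. Minimum hemostatic pressure has no described counterpart in the control arm. Sheath size is treated as variable in four sections and as uniform in a fifth.

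At stake is the soundness of the exploratory results. The pressure interaction, and the sheath interaction if every sheath is 6F, would fail visibly at analysis. The compression-time interaction would give a number, and that number would appear under the label of a prespecified subgroup.

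**Working it through.** **1. The plan's own figures.** Inputs, from Sample size calculation: 4.3% versus 1.0% (4.3% less 3.3%), two-sided alpha 0.05, power 80%, 10% dropout. With unpooled variance:

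n per arm = (1.960 + 0.842)² × (0.043 × 0.957 + 0.010 × 0.990) / 0.033² = 7.849 × 0.05105 / 0.001089 ≈ 368.

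The total is 736, and 736 / 0.9 = 817.8, hence 818. Both figures reproduce, and nothing below alters them.

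**2. Minimum hemostatic pressure.** The intervention procedure titrates in mmHg and records the result. The control procedure works in mL of air with a waveform check and describes no pressure reading. The section on rationale lists the manometer as a component of the new system. On these procedures every patient with a value has treatment = 1. The quartile model has eight columns: intercept, treatment, three quartile indicators and three interactions. Among patients with a value, the treatment column equals the intercept and each interaction column equals its quartile indicator. The rank is therefore 4 of 8, and neither the treatment effect nor the interaction can be estimated.

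**3. Compression time.** The order of events is coronary procedure, patency check, group assignment, compression. Three features make its duration depend on what follows assignment:

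- Each arm has its own decompression schedule.
- Bleeding leads to re-pressurisation or re-inflation in both arms.
- The criteria for discontinuing the allocated intervention allow early removal, for example for pain or signs of ischemia.

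Total hemostasis time, a related measure that counts only active operation and assessment, is itself a secondary endpoint to be compared between arms.

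The model can be fitted here, so the question is what it would show. A simulation with assumed parameters (4,000,000 patients) illustrates this. A standard normal prognostic factor U raises the log-odds of RAO by 1 per unit in both arms, with intercepts set to give 4.3% and 1.0%. Time is 120 + 10U in control and 115 + 2U in intervention, plus noise with SD 4. The conditional odds ratio is constant at 0.21, so there is no effect modification on that scale, and the overall odds ratio is 0.23. Quartiles are taken over both arms together:

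| Quartile of time | RAO, control | RAO, intervention | Odds ratio |
|---|---|---|---|
| 1 | 1.00% | 0.54% | 0.54 |
| 2 | 1.90% | 0.88% | 0.46 |
| 3 | 2.84% | 1.32% | 0.46 |
| 4 | 7.56% | 2.21% | 0.28 |

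Every quartile estimate lies nearer to 1 than the overall odds ratio, and the estimates vary almost twofold (0.54 / 0.28 = 1.9). The longest quartile is mostly control patients (0.217 of 0.250, or 87%). The size of this pattern depends on the assumptions. That such a pattern can arise follows from conditioning on a variable that treatment may affect.

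**4. Sheath size.** If all 818 patients have a 6F sheath, the model has four columns (intercept, treatment, sheath, treatment × sheath). The sheath column equals the intercept and the interaction column equals treatment, so the rank is 2 of 4. If 5F sheaths are used, the variable is set before assignment and is a legitimate subgroup. The two descriptions cannot both be right.

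**5. The remaining variables.** Age, sex, diabetes, and angiography only versus PCI are all fixed before assignment and known in both arms. They are not affected.

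**The case against.** The strongest reply is that little depends on these analyses. Formal inference is reserved for the primary endpoint, and the subgroup section itself warns against definitive interpretation. The pressure problem, and any empty sheath stratum, would show themselves when the model is run. This stands as a limit on severity. It does not cure the defect, because the warning in the subgroup section concerns multiple comparisons. It does not address a variable missing from one arm or a comparison that is no longer randomised.

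Three stronger readings are tempting, and the document does not support them.

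- **That the 5F stratum is certainly empty.** Four sections treat sheath size as variable, and the text on the common procedure may be the inaccurate one. Only reconciliation is warranted. As a covariate, a constant would simply drop out of the adjusted and imputation models.
- **That controls certainly have no pressure value.** The control procedure describes none, but it does not exclude one. The statement holds on the procedures as written.
- **That too few events are expected for any interaction model, so a penalised or risk-difference method is required.** Expected intervention events are 409 × 1.0% = 4.1 (3.7 at 368), about one per quartile. If quartiles split that arm evenly, the chance that at least one has no event is 1 − (1 − 0.99^102)^4 = 0.83 at 409 per arm, and 0.87 with 92 per quartile at 368. This mainly concerns quartile variables that should leave the interaction tests anyway. An infinite coefficient does not rule out a likelihood-ratio test, and sparse-data methods are commonly left to the analysis plan, which is not shown.

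**Conclusion.** The point holds for the two operational variables. The pressure interaction cannot be estimated on the stated procedures (rank 4 of 8), assuming that no pressure is recorded in controls. The compression-time interaction can be computed but is not a valid test of effect modification, because the variable arises after assignment and treatment may affect it. The size of any resulting bias is unknown, and the simulated odds ratios of 0.54 to 0.28 only illustrate it. On sheath size, the finding is a contradiction between sections and goes no further.

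A reader might infer that the trial's main result is in doubt. It is not: the primary comparison, the alpha level and the sample size do not rest on these subgroups. This is a should-fix correction to exploratory analyses.

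**What to change.** 1. Remove compression-time quartiles and minimum-pressure quartiles from the treatment-by-subgroup interaction tests. If these displays are wanted, describe RAO by compression time within each arm, and by pressure in the intervention arm only, labelled as non-randomised.
2. State that interaction tests are confined to variables fixed before randomisation and available in both arms: age, sex, diabetes, angiography only versus PCI, and sheath size only if it varies.
3. Reconcile Common procedural protocol with Subgroup analyzes, Handling of missing data, Analysis of the primary and secondary endpoints, and Modeling and adjusted analyzes. If all sheaths are 6F, take sheath size out of the subgroups, the adjustment set and the imputation model. If 5F sheaths are also used, correct the description of the common procedure and keep the subgroup.

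The cost is a change of wording before analysis and the loss of two exploratory interaction displays. No new data are needed, and the sample size does not change.
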